### Patient level evaluation

#### Patient consultation questionnaire

Eligible participants who consented to medical record review and further contact in the initial baseline patient population survey (see component 2), and who subsequently consult with joint pain in one of the four intervention practices will be identified via fortnightly electronic searches of consultation data and receive a consultation questionnaire asking about their consultation experience with the MOAC intervention. This will also be administered to eligible participants in the four control practices, to enable comparison of patient reported clinical outcomes.

The primary clinical outcome measure for the cluster RCT is the SF12 PCS [40]. The primary follow-up time point is six months. Key secondary outcomes include the Arthritis Self-Efficacy pain subscale [41] and the OMERACT/OARSI responder criteria [42]. Other outcome measures collected in the trial can be found in (Table 2). Participants will be followed up at 3, 6 and 12 months after consultation to determine short, medium and long term behaviours and patterns of the uptake of core OA treatments. Process outcome measures will also be collected within the study (*e.g*., achieving Quality Indicators of care).

**Table 2 Tab2:** **Consultation survey measures**

**Data Collection**	**Measurement Scale**	**Time points**			
		**Baseline**	**3 months**	**6 Months**	**12 Months**
*Demographic Information*					
Age	Years	✓	✓	✓	✓
Gender	Female/Male	✓	✓	✓	✓
Weight	Stones and lbs or Kilograms	✓	✓	✓	✓
*Work related Questions*					
Current/most recent job title	Free Text	✓	✓	✓	✓
Currently in a paid Job	Yes/No/Retired	✓	✓	✓	✓
Typical working week	Working full time (30 hours or more per week)/ Working part time (29 hours or less per week)/	✓	✓	✓	✓
Time off during last 6 months because of joint pain including time off to visit any health care professional	Yes/No	✓	✓	✓	✓
How many days, weeks or months were you absent from work due to joint pains in the last 6 months	Number of days/weeks/months	✓	✓	✓	✓
*Consultations*					
GPAQ communication sub scale [43]	8 – 56	✓			
GPAQ for Nurses communication sub scale (modified GPAQ [43])	8 – 56		✓		
Consulting Practice Nurse (single question)	Yes/No		✓		
*Joint Pain*					
Specific Joint Pain and Problems in knee/hip/hand/foot over 3 months	Yes/No	✓	✓	✓	✓
Pain intensity in the knee/hip/hand/foot over 3 months	0-10 numerical rating scale	✓	✓	✓	✓
WOMAC Physical function subscale [44]	0 - 32	✓	✓	✓	✓
AIMS 2 hand and finger function subscale [45]	0-20	✓	✓	✓	✓
*Physical Activity*					
IPAQ [46]	Categorical score: low, moderate, high	✓	✓	✓	✓
	Continuous score: MET-min per week				
Walking Questions	Where do you regularly walk for reasons including health and well-being?/ Who do you regularly walk with?	✓	✓	✓	✓
PASE [47]	0 – 361	✓	✓	✓	✓
Global Assessment of change [48]	Completely recovered, much better, better, no change, worse, much worse		✓	✓	✓
*General health and Well being*					
PHQ8 [49]	0 – 24	✓	✓	✓	✓
GAD7 [50]	0 – 21	✓	✓	✓	✓
SF12 version 2 [40]	0 – 100	✓	✓	✓	✓
SF6D [51]	0.29-1				
EQ-5D [52]	-0.59-1	✓	✓	✓	✓
ICECAP-A version 2 [53]	4 - 20	✓	✓	✓	✓
*Managing your joint problems*					
Arthritis Self Efficacy pain sub scale [41]	0 - 10	✓	✓	✓	✓
Patient generated OA Quality Indicators (Adapted from Østerås et al [54])	15 questions (Yes/No/Don’t remember)	✓	✓	✓	✓
Medication/Treatment Use (adapted for joint problems from Jinks et al [55])	Simple count of strategies used	✓	✓	✓	✓
Patient Enablement (modified from Howie et al [56])	0 - 10		✓	✓	✓
Healthcare Utilisation	Self-help remedies, contact with NHS and private healthcare, over the counter medicines, prescribed medication			✓	✓

Key:

AIMS 2 = Arthritis Impact Measurement Scale; GAD 7= Generalized Anxiety Disorder 7; GP = General Practitioner; GPAQ = General Practice Assessment Questionnaire;

ICECAP-A = self-report measure of capability wellbeing for adults; IPAQ: International Physical Activity Questionnaire; MET = Metabolic Equivalent; PASE = Physical Activity Scale for the Elderly; PHQ8 = Patient Health Questionnaire 8; EQ5D = Quality of Life; SF12 = Short Form 12; SF6D = Short Form 6D; WOMAC = Western Ontario and McMaster Universities Arthritis Index.

The trial statistician will be kept blind to the practice allocation until after the analysis of the primary and secondary outcomes (blinding will be broken for the per protocol analysis) [43].

### Objectives: Study component 1

To determine the clinical and cost effectiveness of the MOAC intervention in four general practices compared with four control practices using patient reported outcome measures.To train healthcare professionals (GPs and practice nurses) to deliver the MOAC intervention.To implement the MOAC intervention to deliver supported self-management for adults with OA within routine primary care.

### Trial status

Eight general practices have been recruited, and the intervention has been developed and delivered in the four intervention practices. We expect follow-up data collection to be complete in 2014.

### Study component 2: Population survey

A cross sectional population survey will be mailed to an estimated sample of 30,000 adults aged 45 years and over registered in the eight participating general practices participating in the study. After exclusions and based on previous similar studies from the Research Centre, we anticipate a sample of 9,600 with self-reported joint pain.

The population survey will use a 2-stage mailing process based on established procedures conducted in the Arthritis Research UK Primary Care Centre. Eligible participants will be sent a letter of invitation to take part in the survey, information about the study, and the population survey. This survey will collect demographic and work-related data and ask questions regarding general and psychological health, physical activity, joint pain in the last 12 months, consultation behaviour and the management of their joint pain (knee, hip, foot, hand) (the full list of outcome measures can be found in Table 3). Consent will be sought for further involvement in the MOSAICS study and for allowing access to their medical records. Individuals excluded by the GP or contacting the research team and not wishing to take part in the study will be tagged in the practices as exclusions and will not be contacted again for this study. After two weeks, non-responders will be sent a reminder survey and letter.

**Table 3 Tab3:** **Population survey outcome measures**

**Data Collection**	**Measurement Scale**
*Demographic*	
Age	Years
Gender	Female/Male
Marital status	Married/separated/divorced/widowed/cohabiting/ single
Living alone	Yes/No
Spouse/Partner cohabiting	Yes/No
Cost of living	Find it a strain to get by from week to week/Have to be careful with Money/Able to manage without much difficulty/Quite comfortably off
Height	Feet and inches or centimetres
Weight	Stones and lbs or kilograms
*Work related questions to determine occupational social class*	
Employment status	Employed / Not working due to ill health /Retired/ Unemployed or seeking work/ Housewife/Other
Spouse/partner’s job title	Free Text
Work related questions including:	Current employment status; Job title (or previous job title if retired/unemployed); Spouse’s job title (or previous job title if no longer working or deceased)
*General health*	
SF12 version 2 (physical and mental summary score) [40]	0 - 100
GAD7 [50]	0 - 21
EQ-5D 3 level version [52]	-0.59 - 1
*Physical Activity*	
STAR [58]	Three categories: 1) Physically inactive, 2) Meets the current recommendations of physical activity, 3) Insufficiently active
*Joint Pain*	
Specific joint pain and problems in knee/hip/hand/foot over past year	Yes/No
Pain intensity in the knee/hip/hand/foot over past month	0-10
*Managing Joint Problems over the last 12 months*	
Consultation with practice nurse (single question)	Yes/No
Consultation with GP (single question)	Yes/No
Medication/Treatment use (adapted for joint problems from Jinks et al [55])	Simple count of strategies used

GP = General Practitioner; GAD 7 = Generalized Anxiety Disorder 7; EQ5D = Quality of Life; SF12 = Short Form 12; STAR = Short Telephone Activity Rating.

Those that respond to the population survey and agree further contact will be approached for data collection regarding the cluster RCT if they consult with joint pain during the recruitment period. The key reason for doing this is to minimise selection bias in the trial by separating the process of consent from the intervention.

### Objectives: Study component 2

To describe pain severity, general health, psychological status, and uptake of core treatments for OA recommended by NICE in participants aged 45 years and over with joint pain (hip, knee, hand, foot).To identify a population within the practices that agrees to further contact and medical record review and can therefore be approached for data collection for the cluster RCT.

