### Study component 1: The cluster RCT

This will be a two-arm prospective pragmatic cluster RCT based in eight general practices in the North West midlands and Cheshire, UK. This trial will test the hypothesis that the MOAC intervention is superior to control and will be a parallel group longitudinal design with repeated measures. Practices will be randomly allocated to two clusters: ‘intervention’ and ‘control’ practices. Stratified block randomisation will be performed with the practices stratified into four largest and four smallest practices by list size. In each stratum, the practices will be randomly allocated by a computerised random number generator using blocking with two practices per study group.

Recruitment to the trial will occur over a six-month period. All practices will use the OA template and will be given standard information on OA for patients and healthcare professionals published by Arthritis Research UK. In four practices, patients will receive the MOAC intervention, while the other four practices will continue to provide usual care. GPs in the intervention arm will be offered training for the initial consultation (MOAC 1), and practice nurses will be offered comprehensive training for follow-up consultations (MOAC 2), to deliver supported self-management of OA. The control practices will have the opportunity to receive the training at the end of data collection.

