### Study component 3: Consultation template and medical record review

This component will collect anonymised practice-level data to describe the management of OA in primary care via retrospective and prospective medical record review in the eight practices recruited to the study. The OA consultation template will record specific Quality Indicators for the core management of OA which are not routinely recorded in practice. These indicators were established through a systematic review of Quality Indicators of OA [48]. These include pain and functional impairment, provision of information, advice about exercise and weight loss, and advice about pharmacological management such as use of paracetamol and topical non-steroidal anti-inflammatory drugs (NSAIDs).

A download of routine consultation, prescription and other management data related to joint pain and OA will be obtained for the preceding 12 months before the introduction of the template. Data regarding certain co-morbidities, identified as having implications for prescribing behaviours in the management of joint pain and OA, will also be obtained for three years preceding the introduction of the template.

The OA consultation template will then be introduced in all of the eight practices at baseline (six months prior to randomisation of the practices for the cluster RCT described in component 1). Training regarding use of the template as part of routine consultations for patients presenting with a working diagnosis of OA (knee, hip, hand or foot pain) will be provided for the GPs and practice nurses. When a patient aged 45 or over with joint pain consults in any of the eight practices and the GP or practice nurse enters a Read code for OA or one of a selection of joint pain Read codes (see Additional file 4), the OA consultation template will open to allow data entry. The GP or practice nurse undertaking the consultation may complete the template, or bypass the template, as appropriate (for various reasons, such as the joint pain not being related to OA). Data on routine recording of management and Quality Indicators will be collected in the template prospectively at 6 months after baseline and 21 months by downloading anonymised practice data.

### Objectives: Study component 3

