### Analysis

#### Analysis of the cluster RCT

Baseline characteristics will be compared between treatment arms and presented at the level of: (i) GP-Practice clusters, and (ii) Patient characteristics.

Baseline data for GP-Practice characteristics will include data on the stratification variables for randomisation – *i.e*., practice list size and the number of GP practitioners, median index level of deprivation for the Practice, mean age and gender profile of the Practice populations. Baseline data for patients will include data pertaining to participants’ demographic characteristics, joint problem, management of their joint problem, general health and quality of life.

Balance of baseline characteristics is particularly important to establish for cluster trials given the higher level unit of randomisation and thus the potential for bias in the selection and recruitment uptake of patients. No formal statistical testing will be carried out for differences in baseline characteristics except for the GPAQ communication sub scale [49], as this is measure of the uptake of the model OA consultation by GPs.

Descriptive statistics on mean scores for numerical outcomes and frequency counts and percentages for categorical data will be presented for outcome measures from the consultation questionnaire, stratified by study group (intervention or control). A Linear Mixed Model will be used to analyse primary outcome data (SF-12 PCS). Statistical testing of clinical and process outcomes between study groups will be performed using regression methods (adjusting for age, gender, baseline SF12-PCS and corresponding baseline value, of the outcome being measured, as covariates at the individual-patient level and practice size as a covariate at the practice level). A 3-level mixed-model (linear- or generalised- as appropriate to numerical and categorical outcome data, respectively) will be fitted to test for the effect of the MOAC intervention from baseline across follow-up, taking into account clustering by practice (level 3) and patient (level 2) and repeat follow-up measures (level 1). P-values and 95% Confidence Intervals will be provided with estimates of effect size in the analysis of follow up data. The mixed model assumes that missing data is at least missing at random (MAR). We will examine effect estimates in relation to the indicated clinical marker of 0.3 of an effect size.

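### Early survey consent is only a partial safeguard: trial entry is still settled after allocation, and the stated baseline check cannot show who was not identified

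*Protocol article*

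**What the plan says.** All references are to the Protocol article.

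- **Study component 2 (text after Table 3).** Survey responders who agree to further contact "will be approached for data collection regarding the cluster RCT if they consult with joint pain during the recruitment period". The reason given is: "The key reason for doing this is to minimise selection bias in the trial by separating the process of consent from the intervention".
- **Patient consultation questionnaire.** Consenters who later consult with joint pain are "identified via fortnightly electronic searches of consultation data and receive a consultation questionnaire asking about their consultation experience with the MOAC intervention". For the other arm: "This will also be administered to eligible participants in the four control practices, to enable comparison of patient reported clinical outcomes".
- **Study component 1.** "Recruitment to the trial will occur over a six-month period". GPs and practice nurses in the intervention arm are offered training; control staff can have it once data collection ends.
- **Study component 3.** In all eight practices the template opens when "the GP or practice nurse enters a Read code for OA or one of a selection of joint pain Read codes".
- **Table 2.** The trial baseline SF-12 and the GP communication scale (GPAQ) are both baseline items of the consultation questionnaire.
- **Analysis of the cluster RCT.** The article recognises the "potential for bias in the selection and recruitment uptake of patients" and responds by comparing baseline characteristics of practices and patients between arms. The models adjust for age, gender, baseline SF-12 PCS and practice size.

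**The concern.** Consent is only the first of several steps into the trial sample. The later ones are whether the person consults about joint pain, whether that consultation is recorded so that the search finds it, and whether the questionnaire comes back. All can be influenced by what the practice is doing, and one arm has newly trained GPs and a new nurse clinic for OA. If the intervention changes who consults or what is recorded, the primary SF-12 PCS comparison is between differently selected groups, and early consent does not prevent that. A baseline table of entrants cannot reveal it either, because people who were not identified are not in the table.

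**Working it through.** **1. Timing of the entry steps.** The survey precedes the index consultation, since participants are those who consult subsequently. The questionnaire follows that consultation, and in intervention practices it asks about the MOAC consultation, so recruitment there takes place after allocation and after the intervention has started. No single sentence says this; it follows from the passages together. Staff know their arm because one arm is trained. Within the trial, only the statistician is described as blind.

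**2. Can recording differ by arm?** The protocol treats this as an open question of its own: the objectives of components 3 and 4 include changes in recording following the MOAC intervention. An electronic search finds only what was recorded, so running the same search in both arms does not ensure equal detection. That detection depends on Read codes is an inference from the template description; the questionnaire section refers only to consultation data.

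**3. What the stated check can see.** It compares entrants with entrants. The trial baseline comes from the post-consultation questionnaire. The analysis section formally tests baseline GPAQ because it reflects GPs' uptake of the model consultation, so this baseline follows exposure to MOAC 1. Adjustment for baseline PCS is therefore not clearly adjustment for a pre-intervention value. The population survey (Table 3) holds earlier SF-12, pain intensity, GAD7 and age, but the article states no use of them for this check.

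**4. How much selection follows consent.** Planned recruitment is 500; the anticipated number with self-reported joint pain is 9,600. 500 / 9,600 = 5.2%, about 1 in 19. The 9,600 may include people who did not agree to contact, so the share of the consented pool may be higher.

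**5. Reproducing the planning figure, to obtain a standard error.** Inputs from the Sample size section: effect size 0.3, SD 10, two-sided 5%, 90% power, ICC 0.005, coefficient of variation 0.5, factors 0.67 and 1.25. The mean analysed per practice is 400 / 8 = 50.

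- Per arm, unadjusted: 2 × (1.960 + 1.282)² / 0.3² = 233.5
- Design effect: 1 + ((1 + 0.5²) × 50 − 1) × 0.005 = 1.3075
- Per arm: 233.5 × 0.67 × 1.3075 = 204.6, so 409 in total; × 1.25 = 511

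This agrees with the stated 400 and 500 to within 3% and is not in dispute. The effective number per arm is 200 / (1.3075 × 0.67) = 228.3, so the planning standard error is 10 × √(2 / 228.3) = 0.94 points.

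**6. Illustrative bias.** Suppose a share f of intervention-arm entrants is differentially selected and differs by D points on six-month PCS. Neither f nor D is in the documents; both are assumptions. Before adjustment, bias b = f × D. Type I error = Φ(−1.96 − b/0.94) + 1 − Φ(1.96 − b/0.94), by normal approximation. The target is 0.3 × 10 = 3 points.

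| f | D | Bias (points) | Share of 3 points | Type I error |
|---|---|---|---|---|
| 5% | 2 | 0.1 | 3% | 5.1% |
| 10% | 5 | 0.5 | 17% | 8.3% |
| 20% | 5 | 1.0 | 33% | 18.8% |
| 20% | 5, half removed by adjustment | 0.5 | 17% | 8.3% |

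**The case against.** The protocol is more careful than a quick reading suggests. It claims to minimise bias, not remove it, and speaks of consent only. It names the remaining risk itself, plans a balance check and adjusts for age, gender and PCS. Search and questionnaire are the same in both arms, and the template and training in its use reached all eight practices six months before randomisation, which should limit differential coding. All of this stands. A reader might infer that the protocol wrongly claims to have separated recruitment from the intervention; the text does not support that charge.

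A reader might also infer that MOAC 2 nurse clinics give the intervention arm an additional way into the trial. The documents do not establish this. MOAC 2 follows a GP consultation and referral, and that GP visit should already trigger the search. Nurses can enter codes in both arms. Table 2 points to a GP index consultation: GPAQ is asked at baseline, and the nurse items only at three months. What is left is a possibility: the questionnaire section does not limit the search to GP consultations, so a nurse visit might pick up someone whose GP contact was unrecorded or fell outside the window.

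Finally, sensitivity analyses for the primary outcome are in Additional file 5, which is not shown, so it cannot be said that a suitable one is absent. None of this alters the central point: the stated check cannot see people who were not identified, and its baseline is measured after the index consultation.

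**Conclusion.** The point holds in a limited form. Survey consent protects one of several entry steps; the others follow allocation in practices that know their arm, so differential identification remains possible. This is a possibility, not a demonstrated bias. Its size is not fixed by the documents: with the assumed shares (5% to 20%) and differences (2 to 5 points) it ranges from negligible to a third of the target difference, and covariate adjustment would remove an unknown part. The nurse-visit route is unproven, and the conclusion does not depend on it. No change in sample size follows. The case for acting is that a clearly better check is available from data the study already collects.

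**What to change.** 1. In Analysis of the cluster RCT, add a comparison among consenting survey responders with joint pain. By practice and arm, report how many were identified and how many returned the questionnaire. Compare identified with non-identified responders on survey SF-12 PCS, pain intensity, GAD7 and age. Some difference is expected in both arms, because people who consult differ from those who do not; the informative question is whether the contrast differs between arms. With eight practices this should be read descriptively.
2. Unless Additional file 5 already covers it, add a sensitivity analysis of the primary outcome restricted to participants who reported hip, knee, hand or foot pain in the survey, adjusted for survey SF-12 PCS. It brings in a covariate measured before the index consultation. It does not remove differential identification among people with survey-reported pain, so it complements item 1 and does not replace it.
3. In Study component 2, describe the survey step as a partial safeguard that separates consent, but not identification, from the intervention.

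Trial status reports that the intervention has already been delivered, so changing the entry rule is no longer practical; these are changes to analysis and reporting. The cost is a few extra tables, one extra analysis and some participants lost from that analysis.
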